### Trial design {8}

A parallel-group, randomized, placebo-controlled, double-blind superiority trial will be used to determine the effects of 3 weeks of estradiol treatment, relative to placebo, on perimenopausal-onset anhedonia and/or psychosis symptoms and neural and molecular reward responses. The study will enroll 100 participants with at least clinically significant anhedonia, including a range of mild-to-moderate anhedonia and absent-to-moderate psychosis symptoms. Based on screen failures and dropout rates in our prior studies involving PET-MR and perimenopausal depression, we expect to obtain analyzable data from at least 85 participants with two PET-MR scans each.

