### Sample size {14}

For the first study objective, correlation analyses will be used to examine associations between baseline clinical measures (anhedonia and psychosis) and neural markers (striatal BOLD activation and baseline/reward-related dopamine release). Power analysis suggests that a sample of 85 participants will yield approximately 80% power to detect small-to-medium effects (smallest detectible *r*=.27) at *α*=.05, which is consistent with our in-house pilot data. With respect to the study’s second objective, longitudinal mixed models will be used to examine the effects of estradiol versus placebo on (1) symptom trajectories measured across four timepoints and (2) neural/molecular markers across two timepoints. A sample of 85 participants will yield 80% power to detect small-to-medium effects, with the smallest detectible effect *f*^2^=.05 for clinical outcomes and *f*^2^=.07 for brain changes. To determine associations between changes in symptoms and changes in neural/molecular reward response in the estradiol treatment group, intercorrelations will be examined in primary analyses. A sample of 43 participants will yield 80% power to detect medium-to-large effects, with the smallest detectible effect size of *r*=.41.

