## Statistical methods

### Statistical methods for primary and secondary outcomes {20a}

The first objective of this study is to examine baseline (i.e., pre-treatment) associations between anhedonia and psychosis and neural and molecular responses to rewards. Associations between clinical measures and mechanistic outcomes will be estimated via correlation analysis. The second objective is to evaluate the experimental effects of estradiol versus placebo on clinical outcome measures and mechanistic outcomes. Mixed effects models will be used to examine the effects of time, treatment group, and their interaction on clinical outcomes (four timepoints, random intercept and slope) and neural and molecular outcomes (two timepoints, random intercept only), with age as a covariate. A separate model will be generated for each clinical outcome measure (anhedonia and psychosis) and each neural and molecular outcome (activation during reward anticipation and BP_ND_ and task-related ΔBP_ND_ for striatal regions of interest). Exploratory whole-brain analyses will also be conducted for fMRI activation during reward anticipation. Within the estradiol treatment group only, we will examine how biomarkers of reward response predict changes in clinical outcome measures. We will examine intercorrelations between anhedonia or psychosis and neural and molecular reward response, using residualized gain scores to quantify changes in clinical measures. We will also use mixed effect models to examine how changes in neural and molecular reward response predict variability in clinical outcome trajectories, with a separate model for each clinical outcome and each neural and molecular change score. Maximum likelihood estimation will be used in all mixed effect models to accommodate missing data (e.g., SAS proc mixed). When multiple comparisons are conducted to test a hypothesis, appropriate correction will be applied to achieve a corrected *p*-value of 0.05. For clinical outcome hypotheses, both a per-protocol and an intent-to-treat analytic approach (e.g., utilizing all available data, even for participants who did not finish treatment to completion) will be used. For mechanistic hypotheses, a per-protocol approach will be used, including only participants who completed the baseline PET-MR scan, 3 weeks of estradiol treatment, and the post-treatment PET-MR scan.

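### Missing data do not justify maximum likelihood over REML in the mixed models, and ML makes their standard errors slightly too small (about 1.2% at N=85, about 2.4% at n=43)

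*Protocol article*

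**What the plan says.** Section {20a} of the protocol article fixes the estimator and gives the reason for it: "Maximum likelihood estimation will be used in all mixed effect models to accommodate missing data (e.g., SAS proc mixed". The models contain time, treatment group and their interaction, for "clinical outcomes (four timepoints, random intercept and slope) and neural and molecular outcomes (two timepoints, random intercept only), with age as a covariate". Mixed models are also planned within the estradiol group alone, relating change in each neural or molecular marker to the course of each symptom score.

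Two other statements bear on the reason given. The mechanistic hypotheses are analysed per protocol, in participants with both PET-MR scans (section {20a}). Section {20c} rules out imputation.

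On numbers, Trial design {8} says "we expect to obtain analyzable data from at least 85 participants with two PET-MR scans each". Sample size {14} uses 43 for the estradiol group and says of the link between symptom change and marker change there that "intercorrelations will be examined in primary analyses".

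**The concern.** ML estimates the variance components as if the fixed effects were known. In a balanced design it divides the relevant sum of squares by the number of participants, without subtracting the fixed effects estimated from it. The variance, and so the standard error of the interaction, is biased downward. REML removes that bias.

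The stated benefit does not separate the two methods. Both are likelihood methods that use every available visit and are valid under the same missing-at-random assumption. In the mechanistic models, which carry the primary endpoints according to Objectives {7}, the reason hardly applies at all, because the per-protocol rule leaves no scan visit missing.

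At stake is a slightly anti-conservative test in every mixed model, always in the same direction. That covers nine mechanistic models (three measures in three striatal regions), two clinical models and the estradiol-only models.

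**Working it through.** **Inputs.** N = 85 analysable in two arms (Trial design {8}) and n = 43 in the estradiol group (Sample size {14}, where it is given for correlations and serves here only as the group size). The level is 5%, from "appropriate correction will be applied to achieve a corrected" p-value of 0.05; the sidedness is not stated and is taken as two-sided.

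**The plan's own figure.** The article gives no type I error for these models beyond the nominal level. Its power statement for them ("A sample of 85 participants will yield 80% power to detect small-to-medium effects, with the smallest detectible effect" *f*² of .05 clinical and .07 brain) cannot be reproduced, because neither the within-person correlation nor the definition of *f*² is given. The check below does not depend on it.

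**Closed form, complete data.** The interaction is a comparison of per-person changes (two scans) or slopes (four visits), with two fixed effects estimated from N such values. Age as a main effect does not enter. ML divides the sum of squares by N, REML by N − 2, so

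SE ratio = √((N − 2)/N).

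- N = 85: √(83/85) = 0.988, so SEs are 1.2% too small.
- n = 43: √(41/43) = 0.976, so SEs are 2.4% too small.

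The true two-sided size is 2·P(t > critical value × ratio) on N − 2 degrees of freedom:

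| | ML, t | ML, normal | REML, t | REML, normal |
|---|---|---|---|---|
| N = 85 | 5.3% | 5.6% | 5.0% | 5.3% |
| n = 43 | 5.5% | 6.3% | 5.0% | 5.7% |

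The part due to ML is the gap between the ML and REML columns on the same reference. On t, that is about 0.3 points at N = 85 and 0.5 points at n = 43. The normal reference on its own adds at least as much under REML (5.3% and 5.7%).

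If a third fixed effect acted on the slope, such as age by time, the t-based ML figures would be 5.4% and 5.8%.

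**Simulation with missing data.** There were 6,000 null trials per setting, with four visits, random intercept and slope, age as a covariate, 15% random dropout (assumed from 100 enrolled and 85 analysable) and assumed variance components. ML and REML were fitted to the same incomplete records, with t on N − 2 degrees of freedom. The Monte Carlo standard error is about 0.3 points.

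- N = 85: ML 5.3%, REML 5.0%; SE ratio 0.987.
- n = 43: ML 6.1%, REML 5.3%; SE ratio 0.974.

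REML therefore handled the same missing data and stayed within Monte Carlo error of 5%.

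**Multiplicity.** The correction method is not named. Assuming Bonferroni over nine mechanistic tests at N = 85, each test has nominal level 0.05/9 = 0.00556. Under ML with t its actual size is 0.00611, and 9 × 0.00611 = 0.055 in place of 0.050.

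**The case against.** The strongest reply is that the sentence is over-read. Next to the statement that nothing will be imputed, it may only mean that a likelihood method will use all available records, with *maximum likelihood* as a loose label that includes REML. That is possible. The words still name ML for all mixed models, and an unseen analysis plan could not turn to REML without departing from them. If REML was meant, the same edit removes the doubt.

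The reply also says that the effect is negligible for the main comparisons. At N = 85 this stands.

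Three stronger readings are tempting, and the documents do not support them.

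- A reader might infer type I error of 6% to 7%. Apart from the 6.1% simulated at n = 43, which depends on assumed variance components and dropout, such figures need a normal reference, which the article does not state. Much of that excess would remain under REML. The degrees-of-freedom method may be in an analysis plan that is not shown, so its absence is no fault here.
- A reader might infer that the power statement for 43 participants is affected. That statement concerns correlations, with a smallest detectable *r* of .41, and the choice between ML and REML does not touch them. The estradiol-only mixed models come in addition.
- A reader might infer that REML costs nothing. It costs a little nominal power, and REML likelihoods cannot compare models with different fixed effects.

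**Conclusion.** The point holds as a minor improvement. Missing data is not a reason to prefer ML, and ML makes the tests slightly anti-conservative. The sizes given for N = 85 and n = 43 assume two-sided tests, a t reference and, in the closed form, complete data. The n = 43 figure is a balanced-data equivalent and concerns models that are not the primary analysis in that group. Nothing here is likely to change the main estradiol-placebo conclusions.

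**What to change.** Replace the sentence in section {20a} with:

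> Mixed models will be fitted by REML with Kenward-Roger (or Satterthwaite) degrees of freedom, using all available data; ML only for comparing fixed-effect structures.

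The cost is two software options and very slightly larger p-values. Where REML with t has 80.0% power, ML shows 80.6% (t) to 81.4% (normal) at N = 85, and 81.3% to 82.8% at n = 43. Nominal power therefore falls by 0.6 to 2.8 points, which is only what the inflated error had bought. No extra data or participants are needed.

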### Objectives {7}

The primary endpoints of the PEEPs study are mechanistic, measured via neural and molecular reward responses. Using simultaneous PET-MR imaging, this study will examine striatal blood oxygen level-dependent (BOLD) activation to rewards, measured with fMRI, and reward-related striatal dopamine release, measured with [^11^C]raclopride PET. To elicit a reward response, participants will complete a monetary incentive delay (MID) task during imaging. This task has previously shown sensitivity to altered reward-related dopamine release in a transdiagnostic anhedonia sample [35]. The first study objective aims to characterize the relationship between striatal reward responses and perimenopausal-onset anhedonia and psychosis symptoms at baseline. We hypothesize that anhedonia symptoms will be linked to reduced striatal BOLD activation and decreased task-related dopamine release to rewards. In contrast, we expect psychosis symptoms will be linked to increased striatal activation to rewards and higher baseline (tonic) dopamine release. The second objective of this trial will be to determine the effects of estradiol versus a placebo on perimenopausal-onset anhedonia and psychosis symptoms as well as striatal reward responses. We expect the effects of estradiol will be greater than placebo, as indexed by alleviation of anhedonia and psychosis symptoms and normalization of striatal reward response. We further hypothesize that reductions in *anhedonia* symptoms in the estradiol treatment group will be linked to increased striatal activation and increased dopamine release to rewards, whereas reductions in *psychosis* symptoms will be associated with decreased striatal activation to rewards and reduced tonic dopamine release.

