### Outcomes {12}

#### Mechanistic outcomes

The primary mechanistic endpoint in this trial will be neural and molecular response to rewards using simultaneous PET-MR, which will be measured at baseline and at the end of treatment. Scans will be collected on a Siemens Biograph mMR scanner. A whole-brain, T1-weighted MPRAGE image will be collected (1mm isotropic, TR=2400ms, TE=2.13ms). A whole-brain T2*-weighted BOLD sequence will be used for the acquisition of fMRI task data (3mm isotropic, TR=3000 ms, TE=30ms). Simultaneous acquisition of PET data will occur using [^11^C]raclopride PET imaging to estimate D2 and D3 receptor occupancy at baseline and during reward conditions. A bolus plus infusion protocol will be used with the following parameters: K_bol_=70 min, total radioactivity=15 mCi, mass dose=10 μg (specific radioactivity at time of bolus > 0.4 Ci/μmol). Listmode 3D emission data will be acquired from bolus administration through scan duration. The study will also acquire Siemens proprietary MR attenuation maps optimized for head imaging with a bone compartment to be used for attenuation correction.

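### The estradiol-versus-placebo comparison on the primary mechanistic endpoints is planned only in per-protocol completers, with no all-randomised analysis

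*Protocol article*

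**What the plan says.** Objectives {7} states: "The primary endpoints of the PEEPs study are mechanistic, measured via neural and molecular reward responses". The Mechanistic outcomes section repeats this: "The primary mechanistic endpoint in this trial will be neural and molecular response to rewards using simultaneous PET-MR". Trial design {8} sets the inferential frame: "A parallel-group, randomized, placebo-controlled, double-blind superiority trial will be used".

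Statistical methods {20a} gives the second objective as to "evaluate the experimental effects of estradiol versus placebo on clinical outcome measures and mechanistic outcomes". It fits time, treatment group and their interaction to the neural and molecular outcomes at two timepoints, with a random intercept. On estimation it says: "Maximum likelihood estimation will be used in all mixed effect models to accommodate missing data".

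The same section then sets the analysis populations. "For clinical outcome hypotheses, both a per-protocol and an intent-to-treat analytic approach" will be used. For the imaging endpoints: "For mechanistic hypotheses, a per-protocol approach will be used, including only participants who completed the baseline PET-MR scan, 3 weeks of estradiol treatment", together with the post-treatment scan.

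The Compliance monitoring section adds, without limiting it to any outcome, that data are excluded from analysis when a participant has not followed the treatment protocol. The article plans no all-randomised analysis of the mechanistic endpoints.

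**The concern.** The endpoints that the trial calls primary get less protection than the clinical ones. Whether a woman completes treatment, adheres and returns for the second scan is settled after randomisation, and it can depend on which patch she wears and how she responds. The article's own discontinuation rules name such events: non-compliance and suicidal ideation (section {11b}), and starting mood-altering medication (section {11d}). In a trial of estradiol for mood-related symptoms these could plausibly occur at different rates, or in different kinds of women, in the two arms. The compared groups would then no longer be the randomised groups, and a difference in imaging outcome could partly reflect who remained. The bias could favour either arm.

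Information that exists would also go unused: second scans of women judged non-adherent, and baseline scans of women who leave early. A likelihood-based mixed model can use both.

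**Working it through.** **1. What each outcome family gets.**

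| | Clinical outcomes | Mechanistic (primary) outcomes |
|---|---|---|
| Between-arm question | estradiol vs placebo | estradiol vs placebo |
| Model | mixed model, four timepoints | mixed model, two timepoints |
| All-randomised analysis | yes | none |
| Per-protocol analysis | yes | yes, the only one |

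In a two-timepoint model limited to women with both scans, no scan visit is missing. For these models the missing-data rationale for maximum likelihood therefore has nothing to act on. It keeps its purpose for the four-timepoint clinical models.

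**2. The literal wording.** With about 43 estradiol women and no placebo women, the design matrix for intercept, group, time and group-by-time has rank 2. With 43 and 42 it has rank 4. Read literally, the treatment effect cannot be estimated. The Sample size section shows that this is not intended: it counts 85 women for brain changes and 43 for the estradiol group, which leaves 85 − 43 = 42 on placebo.

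**3. How many women.** Trial design {8} plans 100 enrolled and at least 85 with two analysable scans. At most 100 − 85 = 15 women (15%) are therefore affected. The article attributes the shortfall to both screen failures and dropout. Screen failures precede randomisation, and unusable scans need not relate to treatment.

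**4. Illustration of bias (all selection inputs assumed).** Take no true effect, 50 women per arm and 15% lost per arm. A woman is retained if a latent variable, correlated ρ with her brain change, exceeds its 15th percentile (z = −1.036, normal density 0.233). The mean change among those retained is shifted by

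ρ × 0.233 / 0.85 = 0.274ρ SD.

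| ρ estradiol, ρ placebo | Bias, 0.274 × (difference in ρ) | Simulated bias, SD | Simulated type I error (8,000 runs) |
|---|---|---|---|
| 0.3, 0 | 0.082 | 0.081 | 7.0% |
| 0.5, 0 | 0.137 | 0.139 | 9.8% |
| 0.7, 0 | 0.192 | 0.193 | 15.5% |
| 0.5, −0.5 | 0.274 | 0.272 | 25.7% |
| 0.5, 0.5 | 0 | about 0 | 5.3% |

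**5. How much of that an all-randomised analysis would remove.** This depends on why the woman was excluded.

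- *Lost on the unseen change, no second scan.* Maximum likelihood recovers only what the baseline scan predicts. With baseline-to-post correlation r and equal variances, the squared correlation between baseline and change is (1 − r)/2, so the share of bias that survives is roughly 1 − (1 − r)/2 = (1 + r)/2. That is 0.65, 0.75 and 0.85 for r = 0.3, 0.5 and 0.7. Simulation at ρ = (0.5, 0) and r = 0.5 agrees: bias falls from 0.138 to 0.104 SD, and 0.104/0.138 = 75% remains.
- *Lost depending on the observed baseline scan.* With selection 0.5 in the estradiol arm only and r = 0.5, the completer comparison is biased by 0.07 SD. A likelihood-type estimate that keeps baseline-only women is essentially unbiased.
- *Scanned twice but excluded as non-adherent.* Including these women removes the selection. If half of the excluded women have a second scan (selection 0.5), bias falls from 0.13 to 0.06 SD. If all have one, it vanishes.

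**The case against.** The trial is openly mechanistic: it asks what estradiol does to the reward system when it is received, and a per-protocol estimate is a reasonable answer. Treatment lasts only three weeks, which limits dropout. Section {20c} commits to reporting withdrawal and loss to follow-up by arm, so differential attrition would be visible. All of this stands. It supports keeping the per-protocol analysis, above all for the biomarker–symptom correlations within the estradiol group. It does not justify having no all-randomised analysis of the primary endpoints in a trial declared as a randomised superiority comparison; reporting attrition shows an imbalance but does not correct for it.

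Some stronger readings are tempting, and the article does not support them:

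- *That the plan compares estradiol with nobody.* The treatment-by-time model and the counts of 85 and 43 show that a two-arm set is meant. The phrase is a drafting slip.
- *That this is an as-treated analysis.* Nobody is reassigned by treatment received. It is a per-protocol completer analysis.
- *That the primary result is necessarily biased.* Comparability is no longer guaranteed, but identical selection in both arms gives no inflation.
- *That the simulated error rates measure what the fix would gain.* They assume loss driven by the unseen change and treat all 15 expected losses as occurring after randomisation. Nothing in the article supports the opposite selection behind the 26% figure.

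**Conclusion.** The point holds as a stated choice of analysis set, not as an omission that an analysis plan might fill. The between-arm test on the primary endpoints is restricted to women selected by post-randomisation events, while the clinical outcomes also keep an all-randomised analysis. The number affected is unknown, with a ceiling of about 15 in 100. The direction and size of any bias depend on reasons for loss that the article does not give. Under the assumed correlations the bias is 0.08 to 0.27 SD, and type I error is 7% to 26% against a nominal 5%. These figures are illustrative. An all-randomised analysis helps fully for women scanned twice but excluded as non-adherent, and for dropout that depends on the observed baseline scan. It helps only partly where the second scan is missing for reasons tied to the unseen change.

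**What to change.** In section {20a}:

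1. Make the primary mechanistic comparison an analysis of all randomised women by assigned arm, using every available scan in the mixed model already specified, fitted by maximum likelihood. This includes women with a baseline scan only and second scans from non-adherent women.
2. Keep the per-protocol set as supportive, and for the within-estradiol correlations. Define it as completing three weeks of the assigned treatment, estradiol or placebo, plus both scans.
3. Reconcile the Compliance monitoring section with the intent-to-treat statement, so that its exclusion of data applies to the per-protocol set only.

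The cost is about a paragraph of wording and one extra model run per mechanistic outcome, with no new scans. The downside is slight dilution of the estimate by non-adherent women. The change should be made before any unblinded analysis.

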#### Relevant concomitant care permitted or prohibited during the trial {11d}

To be eligible to complete the study, participants must not be taking any psychotropic medication or supplement that is known to alter the mood. Study participants who elect to begin taking such medications or supplements during the 3-week treatment window will be discontinued from the study.

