### Compliance monitoring

Treatment compliance will be assessed via participant self-report. Blood samples will also be collected on a weekly basis as a biological measure of compliance. Samples will be used to measure serum estradiol levels using the enzyme-linked to immunosorbent assay (ELISA). In the event the study treatment protocol is not followed, the participant’s data will be excluded from analyses.

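### The primary mechanistic endpoints have only a per-protocol completer analysis with a misworded set, and the blanket exclusion of non-adherent women contradicts the clinical intention-to-treat analysis

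*Protocol article*

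**What the plan says.** Objectives {7} states: "The primary endpoints of the PEEPs study are mechanistic, measured via neural and molecular reward responses". Trial design {8} describes the study thus: "A parallel-group, randomized, placebo-controlled, double-blind superiority trial will be used to determine the effects of 3 weeks of estradiol treatment, relative to placebo". Statistical methods {20a} confirms that the mechanistic endpoints belong to the between-arm comparison: "The second objective is to evaluate the experimental effects of estradiol versus placebo on clinical outcome measures and mechanistic outcomes". The model named there has time, treatment group and their interaction, with two timepoints for the brain outcomes.

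The same section then sets the analysis populations. Clinical outcomes get both a per-protocol and an intention-to-treat analysis, the latter on all available data. Mechanistic outcomes get the per-protocol set alone, defined as "including only participants who completed the baseline PET-MR scan, 3 weeks of estradiol treatment, and the post-treatment PET-MR scan". It also says: "Maximum likelihood estimation will be used in all mixed effect models to accommodate missing data".

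Compliance monitoring relies on self-report and weekly serum estradiol. It says of a participant who departs from the treatment protocol that her "data will be excluded from analyses". The sentence is not limited to the per-protocol set or to the mechanistic outcomes. On prohibited mood-altering treatments, section {11d} adds: "Study participants who elect to begin taking such medications or supplements during the 3-week treatment window will be discontinued from the study".

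**The concern.** In a superiority trial, randomisation protects the comparison only if women are analysed in the arm to which they were assigned. Here the primary endpoints are the ones without such an analysis. The set is defined by events after randomisation: finishing treatment, attending the second scan and being judged compliant. Some of the reasons for leaving, in {11b} and {11d}, are tied to symptoms. Serum estradiol can confirm that a patch was worn only in the active arm, so exclusions for non-compliance could differ between arms.

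Two rules also clash. A non-adherent woman cannot be both excluded from analyses and included in a clinical intention-to-treat analysis. And if both scans are required, the maximum-likelihood provision has little left to do in the two-timepoint models. What is at stake is whether a difference in the primary endpoints can be attributed to estradiol rather than to who remained in the set.

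**Working it through.** **1. The passages side by side.**
- The {20a} model needs both arms, while the {20a} mechanistic set requires completed estradiol treatment. The two agree only if the set means assigned treatment.
- Intention-to-treat in {20a} covers clinical outcomes and includes women who did not finish treatment. Compliance monitoring removes non-adherent women without restriction. The two conflict.
- Maximum likelihood in {20a} can use a woman with one scan. The completer set removes her.

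**2. The plan's own numbers.** Trial design {8} expects at least 85 of 100 women with two scans, so up to 15% lost: 85/(1 − 0.15) = 100. Sample size {14} gives a smallest detectable r of .27 at n = 85. By Fisher's z, r = tanh[(z_α + z_power)/√(n − 3)] with 80% power:
- one-sided 0.05: tanh[(1.645 + 0.842)/√82] = .268, which reproduces .27;
- two-sided 0.05: tanh[(1.960 + 0.842)/√82] = .300.

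For brain changes it gives f² = .07. With 85 women and one numerator degree of freedom, power is 0.67 two-sided and 0.78 at α = 0.10. The article states neither sidedness nor the within-person correlation, so this figure cannot be settled. None of these figures decides the point about the analysis set.

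**3. Possible bias from the completer rule.** Assumptions:
- 50 women per arm, no true effect;
- exclusion of a fraction d of an arm follows a latent normal variable that correlates ρ with the outcome change.

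The mean change among those kept shifts by ρ·φ(z)/(1 − d) SD, where z is the normal quantile of 1 − d. The bias is the difference between arms.
- d = 0.20: φ(0.842)/0.80 = 0.350
- d = 0.10: φ(1.282)/0.90 = 0.195
- d = 0.15: φ(1.036)/0.85 = 0.274

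Type I error uses a two-sided 0.05 z-test with SE = √(1/n_E + 1/n_P). For 40 and 45 women kept, SE = 0.217.

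| Loss, estradiol / placebo | ρ, estradiol / placebo | Bias (SD) | Type I error |
|---|---|---|---|
| 15% / 15% | 0.3 / 0.3 or 0.5 / 0.5 | 0 | 5.0% |
| 20% / 10% | 0.3 / 0.3 | 0.3 × 0.155 = 0.05 | 5.5% |
| 20% / 10% | 0.5 / 0.5 | 0.5 × 0.155 = 0.08 | 6.5% |
| 20% / 10% | 0.3 / 0 | 0.3 × 0.350 = 0.105 | 7.7% |
| 20% / 10% | 0.5 / 0 | 0.5 × 0.350 = 0.175 | 12.7% |

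Equal loss alone does not guarantee zero bias: at 15% in each arm with ρ = 0.5 in one arm and 0 in the other, it is 0.5 × 0.274 = 0.14 SD. For scale, f² = .07 on the usual two-group reading is d = 2√.07 = 0.53.

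**4. First objective.** It needs baseline data only, yet {14} powers it on 85, the number expected to have two scans. Two-sided, the smallest detectable r is .300 at n = 85 and tanh(2.802/√97) = .277 at n = 100.

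**The case against.** A mechanistic trial asks what estradiol does when it is taken, so a per-protocol analysis is a natural choice. That supports keeping it, but not as the only analysis: completers in the two arms need not be comparable, so the completer contrast does not isolate that effect.

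Several stronger readings are tempting and are not supported.
- A reader might infer that the placebo arm is left out by design. The model with a treatment-group term shows otherwise; this is a wording error.
- A reader might infer that the mechanistic completer rule contradicts the intention-to-treat statement. It does not, because that statement covers clinical outcomes only. The contradiction lies in Compliance monitoring.
- A reader might infer that one arm will lose more women. The documents do not show this. Self-report applies to both arms, the coordinator places patches weekly, and no serum threshold is given. A raised level could also flag a placebo participant using prohibited hormones.
- A reader might infer that discontinuation leaves intention-to-treat without data. Clinical assessments made before discontinuation exist and enter the model, and {18b} offers home or video visits for clinical measures. What stays open is whether collection continues after discontinuation.

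It also stands that maximum likelihood retains some use, since a completed scan may be unusable, and that a baseline-only woman adds little to a two-timepoint treatment-by-time estimate.

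**Conclusion.** The point holds as a fault in stated rules, and these should be corrected before analysis. The primary endpoints of a randomised superiority trial have no as-randomised analysis, the sentence defining their set is misworded, and the unrestricted compliance exclusion contradicts the clinical intention-to-treat analysis.

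The size is conditional. Bias is zero when loss and its link to outcome match across arms, and about 0.05 to 0.18 SD (type I error 5.5% to 12.7%) with 20% versus 10% loss and ρ of 0.3 to 0.5 in both arms or in the estradiol arm only. Against d of about 0.53 that is roughly 9% to 33% (0.046/0.53 to 0.175/0.53). Arm-dependent exclusion is possible, not demonstrated. The effect on the first objective is modest: detectable r of about .30 instead of .28.

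**What to change.** 1. Make the primary mechanistic analysis the planned maximum-likelihood mixed model on all randomised women with usable scan data, by assigned arm.
2. Keep per-protocol as supplementary, defined as three weeks of the assigned patch, estradiol or placebo, with both scans.
3. Limit the exclusion in Compliance monitoring to the per-protocol set, and apply one compliance criterion identically in both arms.
4. State that the first objective uses every woman with a usable baseline scan and baseline SHAPS and BPRS.
5. Reconcile {11b} and {11d} with the intention-to-treat statement by saying whether outcome data are still collected after discontinuation. The clinical stopping rules themselves need no change for this.

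Items 1 to 4 cost wording only, and Trial status has recruitment open until December 31, 2026. The estimate may be slightly diluted by non-adherence. Maximum likelihood with baseline-only women does not remove selection that depends on the unobserved change; only an end scan would address that. Such scans in discontinued women cannot be done remotely and would alter current discontinuation practice, so they are a separate decision with a real cost.
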